## Abstract

**Background:**

Prevention, or slowing the progression, of diabetic nephropathy is one of the important goals in diabetes care. Although the impact of depression is a concern in patients with diabetes, it is unknown whether there is an association between adherence to hypoglycemic medication and the decline of renal function in comorbid patients with diabetes and depression. We will conduct a cohort study aimed at examining (1) depression as a predictor of renal function decline, and (2) how adherence to hypoglycemic medication relates to depression and renal function decline in patients with type 2 diabetes.

**Methods/Design:**

In this multicenter cohort study, 550 patients with type 2 diabetes aged 20 years and older will be recruited at 20 outpatient clinics in general medicine and psychiatry. We will measure depression (Patient Health Questionnaire), medication adherence (medication possession ratio, Morisky Medication Adherence Scale, and one-item hypoglycemic medication adherence scale), and renal function (urinary albumin-creatinine ratio and estimated glomerular filtration rate) at baseline and at the 12-month follow-up. The primary endpoint is decline of renal function at 12 months. The secondary endpoints include clinical variables, quality of life, and the attitude of professionals toward depression. We will perform multivariable linear regression analysis to evaluate the effects of medication adherence on the decline of renal function in comorbid patients with type 2 diabetes and depression.

**Discussion:**

To our knowledge, this will be the first study to examine how adherence to hypoglycemic medication relates to the decline of renal function in comorbid patients with type 2 diabetes and depression. The results of the study will have implications for practitioners of diabetes care, policy makers, and researchers for the prevention and treatment of diabetic nephropathy.

**Trial registration:**

UMIN000017513 (Registered on May 22, 2015)

## Background

Prevention, or slowing the progression, of diabetic nephropathy is one of the important goals in diabetes care [1, 2]. As the kidney disease progresses, end-stage renal disease (ESRD) occurs and requires either dialysis or transplantation, which places significant burden on the patient and the society. Diabetes is one of the predictors of a poor perceived quality of life in patients with ESRD [3], and the prevalence of diabetes could impose an increasing economic burden due to substantial costs for patients with ESRD [4].

Depression is observed in approximately 20 % of patients with diabetes [5, 6]. Although adherence to hypoglycemic medication is important for the prevention and management of diabetic nephropathy [2], a meta-analysis indicates that depression is associated with lower adherence to hypoglycemic medication in patients with diabetes [7]. Furthermore, depression also adversely affects adherence to other key medications for hypertension and hyperlipidemia - the main risk factors of diabetic nephropathy [8]. Considering the high prevalence of depression and that depression is rather commonly undiagnosed in patients with diabetes [9], the impact of depression on diabetic nephropathy is a growing concern.

The literature has reported the morbidity and mortality of kidney disease in patients with depression. A recent meta-analysis showed that depression was observed in 21.4 % of patients in chronic kidney disease (CKD) stage 1–5 [10]. Comorbid patients with diabetes and depression had higher risks of microalbuminuria [11] and ESRD than those without depression [12]. Patients with diabetic nephropathy who have had a depressive episode were more likely undergo dialysis than those without a depressive episode [13], and the mortality was 1.5-fold higher in diabetes patients with depression than in those without depression [14, 15].

In patients with type 2 diabetes, we aim to examine (1) depression as a predictor of renal function decline, and (2) how adherence to hypoglycemic medication relates to depression and renal function decline.

## Methods/design

### Study design

This is a multicenter cohort study. We refer STROBE reporting guidelines to this protocol (http://www.strobe-statement.org/).

### Ethical approval

The study protocol was approved by the institutional review board (IRB) of the National Center of Neurology and Psychiatry (NCNP) and participating clinics with IRBs. The IRB of the NCNP approved the protocol for those without IRB. This study is in accordance with the Ethical Guidelines for Epidemiological Research (http://www.niph.go.jp/wadai/ekigakurinri/guidelines.pdf).

### Study setting

This multicenter study will be conducted at 20 outpatient clinics (NCNP, 5 from the Japan Diabetes Mellitus Effective Network System, and 14 from the Stress-Care Inpatient Care Network) in Japan. The Japan Diabetes Mellitus Effective Network System is a network of primary care physicians and specialists of diabetes collaborating to prevent diabetes complications, whereas the Stress-Care Inpatient Care Network consists of leading psychiatrists aiming to improve the quality of psychiatric care for patients with depression.

### Participants

All patients who meet inclusion criteria during the study period will be invited to participate in the study. Participants will be eligible for the study if they (1) are 20 years and older, (2) outpatients with type 2 diabetes receiving hypoglycemic medications, and (3) can complete a questionnaire in Japanese. Patients will be excluded if they (1) have cognitive impairment, (2) are pregnant, and (3) have severe disease of the adrenal glands, liver dysfunction, or severe renal impairment (serum creatinine ≥ 2.0 mg/dL).

Eligible patients will be approached by physicians at each site. After an explanation of the study, written informed consent will be obtained from each patient. Patients will be able to access research staff members who are not in charge of their treatment to withdraw from the study at any time.

### Study endpoints

The primary outcome is the decline of renal function in four subtypes categorized according to depression and adherence (depression/adherence: +/−, +/+, −/+, −/−) at 12 months. The secondary outcomes include clinical variables, quality of life, and attitude of physicians toward depression. We assess physician attitudes to depression to confirm no effects of the attitudes on primary outcome in a sensitivity analysis. Previous systematic review suggests necessity for cohort studies to examine information on patients with multimorbidity across all ages and socioeconomic groups [16]. Although analyses of secondary outcomes will be underpowered, we include the analyses in the protocol for confirmation of the analysis of primary outcome and implication for the future studies.

### Data collection

Data will be collected at routine clinic visits by coordinating staff at baseline and 12 months. The data include patients’ demographic variables (e.g., age, gender, and smoking status), body mass index, prescription, blood pressure, laboratory data (e.g., glucose level, HbA1c, total cholesterol, low- or high-density lipoprotein cholesterol, triglycerides, serum creatinine, and urinary albumin-creatinine ratio [ACR]), and diabetic complications. Table 1 shows the primary measures and timings for measurement.

**Table 1 Tab1:** Measures and timings for measurements

	Scale	Baseline	1 Year
Renal function	urinary albumin-creatinine ratio (ACR) estimated glomerular filtration rate (eGFR)	●	●
Depression	Patient Health Questionnaire (9-item): PHQ-9	●	●
Adherence	Medication Possession Ratio (MPR) Morisky Medication Adherence Scale (MMAS-8) Oral Hypoglycemic Agent (OHA) adherence	●	●
Quality of life	EuroQol	●	●

### Renal function

Renal function will be assessed on the basis of ACR and estimated glomerular filtration rate (eGFR) [17, 18], and the decline of renal function is defined as ACR ≥ 30 mg/g creatinine and eGFR < 60 mL⋅min^−1^⋅1.73 m^−2^.

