### Sample-size calculations

We calculated sample size as 550 patients (165 for the depression group and 385 for the non-depression group) having (1) a 30 % prevalence of depression, (2) 10 % difference in microalbuminuria rate (18 % in the depression group and 8 % in the non-depression group), and (3) an 88 % chance of detecting a true difference in microalbuminuria at the 5 % level of significance. Calculation was based on the chi-square test with continuity correction and we did not take into account of adherence since it might be an intermediate variable. The prevalence of depression in patients with diabetes was 20 % in previous studies [5, 6, 10, 11]; however, we estimated 30 % owing to the inclusion of patients from psychiatric clinics in our study. The prevalence of microalbuminuria was estimated by using the data of the Japanese Society of Nephrology [18] and those from a previous study [11].

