### Data analysis

We will use multivariable linear regression analysis to evaluate the effects of medication adherence of comorbid patients with type 2 diabetes and depression on the decline of renal function. We will consider other potential confounding factors including smoking, hypertension, hyperlipidemia, and HbA1c. The risk of decline of renal function will be estimated for four groups by adherence (+/−) and depression (+/−) by odds ratio and 95 % confidence interval.

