## Discussion

To our knowledge, the present study will be the first study to examine how adherence to hypoglycemic medication relates to the decline of renal function in comorbid patients with type 2 diabetes and depression. Given the prevalence of diabetes and depression, the impact of the comorbidity of these diseases is increasingly important. We will use all standardized measures. Renal function is assessed by urinary ACR and eGFR. As an increase of ACR is observed earlier than a decrease of eGFR in CKD, our study design aids in the better understanding of renal function decline from the early phase in comorbid patients with type 2 diabetes and depression. Adherence is assessed by both objective (MPR) and subjective (MMAS-8 and OHA) measures. MMAS-8 measures general adherence to medication, whereas OHA specifically measures adherence to hypoglycemic medication. A wide range of outcomes, including clinical variables, quality of life, and attitude of professionals toward depression, are also assessed.

This study design has several limitations. First, the participants will be patients who regularly visit clinic, causing a risk of bias. This might limit the generalizability of the findings. Second, our study will not include all possible confounding factors related to diabetes, depression, hypoglycemic medication adherence, and decline of renal function; nevertheless, we plan to control the major potential confounding factors.

The results of the present study will have implications to practitioners in diabetes care, policy makers, and researchers for screening a group of patients at a high risk for diabetic nephropathy (i.e., comorbid patients with type 2 diabetes and depression plus poor adherence to hypoglycemic medication) and for the development of intervention strategies for the prevention and treatment of diabetic nephropathy.

In conclusion, the results of this protocol study will indicate the importance of depression in diabetic care through exploring (1) depression as a predictor of renal function decline, and (2) how adherence to hypoglycemic medication relates to depression and renal function decline. Our research will provide insights to all clinicians who encounter comorbid patients with diabetes and depression in dairy practice.

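### The primary outcome, decline of renal function, is a 12-month threshold status without a baseline element; a baseline-adjusted continuous analysis fits the aims better, though its power gain is model-dependent

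*Protocol article*

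**What the plan says.** All references are to the protocol article.

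- **Data collection and Table 1:** "Data will be collected at routine clinic visits by coordinating staff at baseline and 12 months". Both ACR and eGFR are marked for both visits.
- **Renal function:** "and the decline of renal function is defined as ACR" of 30 mg/g creatinine or more, joined by *and* to eGFR below 60 mL/min/1.73 m². No baseline value enters the definition.
- **Study endpoints:** decline at 12 months, across four depression-by-adherence groups, is the primary outcome.
- **Sample-size calculations:** the groups are "165 for the depression group and 385 for the non-depression group", the microalbuminuria rates are "18 % in the depression group and 8 % in the non-depression group", and the stated power is 88% at the 5% level. "Calculation was based on the chi-square test with continuity correction". Adherence was not taken into account.
- **Data analysis:** multivariable linear regression is named first. Then: "The risk of decline of renal function will be estimated for four groups by adherence" and depression, as odds ratios.
- **Discussion:** because ACR rises before eGFR falls, "our study design aids in the better understanding of renal function decline from the early phase".

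**The concern.** The stated aims concern decline, and the Discussion stresses its early phase. The outcome as defined records where a patient stands at 12 months relative to two fixed cuts. Three things follow.

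1. A patient already past both cuts at baseline is counted as having declined, even with no change. The exclusion at serum creatinine of 2.0 mg/dL or more does not by itself remove every patient with eGFR below 60 and ACR of 30 or more.
2. Movement on one side of the cuts is invisible. ACR going from 6 to 28 mg/g, or eGFR from 95 to 65, counts as no decline. Because both criteria must be met, even a rise in ACR past 30 is not counted while eGFR stays at 60 or above. That is the early change the Discussion wants to see.
3. A yes/no outcome reported by odds ratio does not match a linear regression, so the scale of the primary analysis is unsettled.

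Dichotomising also usually costs precision. That matters most in the four-group comparison, whose groups are smaller than the two used to size the study.

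**Working it through.** **Inputs from Sample-size calculations:** n1 = 165 (depression), n2 = 385 (no depression), p1 = 0.18, p2 = 0.08, 5% level (two-sided reproduces the stated power). The rates are for microalbuminuria, that is, ACR alone.

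**Step 1: reproduce the plan's 88%.**
- Pooled rate = (165 × 0.18 + 385 × 0.08)/550 = 0.11.
- Null SE = √[0.11 × 0.89 × (1/165 + 1/385)] = 0.0291.
- Alternative SE = √[0.18 × 0.82/165 + 0.08 × 0.92/385] = 0.0330.
- Continuity correction = ½(1/165 + 1/385) = 0.0043.
- Power = Φ[(0.10 − 0.0043 − 1.96 × 0.0291)/0.0330] = Φ(1.17) = 87.9%. Exact enumeration gives 88.6%.
- Without the correction: 90.4% by approximation, 91.3% exact.

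The stated figure reproduces.

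**Step 2: information kept by a cut.** Under a normal model this is φ(z_p)²/[p(1 − p)]. At p = 0.11 it is 0.188²/(0.11 × 0.89) = 36%. At 8% it is 30%, and at 18% it is 47%.

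**Step 3: power on the continuous scale.** Added assumption: log ACR is normal with the same SD in both groups.
- Implied shift = z(0.92) − z(0.82) = 1.405 − 0.915 = 0.490 SD.
- SE of the mean difference in SD units = √(1/165 + 1/385) = 0.0930.
- Power = Φ(0.490/0.0930 − 1.96) = Φ(3.30) = 99.95%.
- Gain: 99.95 − 87.9 = about 12 points against the stated test; 99.95 − 90.4 = about 9.6 against the uncorrected test; 99.95 − 91.3 = about 8.7 against its exact version. Part of the 12 points (90.4 − 87.9, about 2.4 before rounding) therefore comes from the continuity correction and not from dichotomising.

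**Step 4: relax the equal-SD assumption, holding 18% vs 8%.** With depression-group SD = s, the shift is 1.405 − 0.915s and the SE is √(s²/165 + 1/385).

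| SD ratio s | Shift | Continuous power |
|---|---|---|
| 1.0 | 0.490 | 99.95% |
| 1.1 | 0.398 | 97.9% |
| 1.2 | 0.307 | 82.2% |
| 1.3 | 0.215 | 47.5% |

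If only a subgroup of the depressed patients shifts, by 1.5 to 3 SD, continuous power is 80–88%, so there is no gain.

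**Step 5: the joint outcome.** Steps 1 to 4 use ACR-only rates. The defined outcome also needs eGFR below 60, so it cannot be more frequent, and no rate for it is given. If an assumed 75%, 50% or 25% of ACR-positive patients in each group also meet the eGFR criterion, the continuity-corrected power is about 76%, 57% or 30%.

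**Step 6: what baseline adjustment does.** Suppose the 12-month gap is 0.490 SD, a fraction g of it was present at baseline, and the baseline-to-12-month correlation is r. The adjusted contrast is then 0.490 × (1 − rg), and the residual SD is √(1 − r²). With g = 1 and r = 0.5, 0.7 or 0.8, power is about 86%, 60% or 42%. With g = 0.5 it stays above 99% at each r. Neither g nor r is in the document.

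**The case against.** The strongest reply is that the size of the loss is not the plan's own. The article gives two proportions and no mean, SD, distribution or correlation for either marker, so any continuous-scale power rests on an added model. **This stands.** A reader might infer that dichotomising costs at least 10 points of power on the plan's figures. The document does not support that. Even under the favourable model the like-for-like loss is just under 10 points, and under unequal SDs or a subgroup shift it can vanish or reverse.

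Two further limits also stand. The 18% and 8% describe ACR alone, so the comparison does not measure the loss from the joint definition. And an illustrative four-group calculation would need an adherence split and an adherence effect that the article does not give, so none is relied on here.

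Next, linear regression is already named, so a continuous analysis may be intended. That is possible. But the outcome that is defined is yes/no and the four-group result is an odds ratio, so the text does not settle the scale. It would also be too strong to say that the plan has firmly excluded a continuous analysis.

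Finally, the cited sources may give a reason for the cuts, and the article is condensed. They may well justify the cuts as markers of kidney disease. That would not turn a 12-month status into a measure of decline. If either criterion alone was meant to suffice, crossing the ACR cut would count, but the missing baseline element would remain.

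**Conclusion.** The point holds on the definition and only conditionally on power. The part that needs no assumption is that a one-time threshold status ignores baseline values already being collected. It counts unchanged patients as declining, misses a rise in ACR while eGFR is preserved, and does not match the named regression. It therefore serves the stated aims poorly.

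The power gain of roughly 9–12 points (about 99.9% against 88–91%) rests on a normal log ACR with equal SDs, on ACR-only rates, and on an unadjusted two-group comparison. It is an illustration and not a minimum: 82% at an SD ratio of 1.2 and 48% at 1.3 fall below the binary figure. It is also not the power of the baseline-adjusted analysis recommended here, which cannot be computed from the document. The change is worth making mainly because it aligns the outcome with the question. Confidence is moderate.

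**What to change.** - Make the primary analysis the linear regression already named, with 12-month log(ACR) as outcome, adjusted for baseline log(ACR) and the listed confounders, on depression, adherence and their interaction. Report four-group adjusted geometric-mean ratios with 95% CIs.
- Analyse 12-month eGFR adjusted for baseline eGFR in the same way.
- Keep the threshold status with odds ratios as a secondary summary.
- State in Sample-size calculations that the 88% applies to the binary, ACR-only comparison of depressed with non-depressed patients.

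**Cost.** No new visits, patients or measurements are needed, but this is more than a wording change: the primary outcome and its link to the sample size must be restated. The headline result is less direct for clinicians than an odds ratio. The contrast becomes the 12-month value given baseline, so whatever part of a depression gap was present at baseline and carries forward is removed. In a non-randomised cohort that is a different question from the 12-month difference itself, and the protocol should say that it is the one intended.

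### Renal decline is defined as a 12-month level with no reference to baseline, so as written it counts unchanged patients who already met it at entry

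*Protocol article*

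**What the plan says.** All references are to the protocol article.

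- **Aim (Background).** The first aim is to examine "depression as a predictor of renal function decline".
- **Endpoint (Renal function; Study endpoints).** "the decline of renal function is defined as ACR ≥ 30 mg/g creatinine and eGFR < 60" (mL/min/1.73 m²). Study endpoints adds the grouping, "The primary outcome is the decline of renal function in four subtypes categorized according to depression and adherence", and the 12-month time point.
- **Eligibility (Participants).** The only renal exclusion is "severe renal impairment (serum creatinine ≥ 2.0 mg/dL". There is no limit on ACR or eGFR at entry.
- **Measurement (Data collection).** "Data will be collected at routine clinic visits by coordinating staff at baseline and 12 months". Table 1 lists ACR and eGFR at both times.
- **Analysis (Data analysis).** "We will consider other potential confounding factors including smoking, hypertension, hyperlipidemia, and HbA1c". Also, "The risk of decline of renal function will be estimated for four groups by adherence" and depression, by odds ratio with a 95% confidence interval.
- **Sample size (Sample-size calculations).** "550 patients (165 for the depression group and 385 for the non-depression group", for microalbuminuria of 18% against 8%, with 88% power at the 5% level. The section describes the source figures as prevalences.

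**The concern.** The aim is longitudinal, but the endpoint is a state at one time. A patient who enters with ACR of at least 30 and eGFR below 60 and stays there is counted as declined. So is one who improves but remains past both cut-offs. A patient whose eGFR falls a long way but stays above 60 is not counted.

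The 12-month comparison therefore mixes disease present at entry with disease that developed during follow-up. If depressed and non-depressed patients differ in kidney disease at entry for any reason, including kidney disease leading to depression, that difference is carried into the primary result and read as depression predicting decline. The reverse error is also possible: prevalent cases shared by both groups dilute a real difference in new onset.

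**Working it through.** **1. The plan's own figure.** Inputs from Sample-size calculations: n = 165 and 385, 18% and 8%, 5% level (taken as two-sided), chi-square with continuity correction.

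- Pooled rate = (165 × 0.18 + 385 × 0.08)/550 = 0.11
- SE under the null = √[0.11 × 0.89 × (1/165 + 1/385)] = 0.0291
- SE under the alternative = √[0.18 × 0.82/165 + 0.08 × 0.92/385] = 0.0330
- Correction = ½(1/165 + 1/385) = 0.0043
- Power = Φ[(0.10 − 0.0043 − 1.96 × 0.0291)/0.0330] = 87.9%; exact power of the corrected test is 88.6%

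The stated 88% reproduces. The arithmetic is not in dispute, but the 18% and 8% derive from prevalences, so the figure describes a contrast in prevalence.

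**2. What the definition does when depression has no effect on new onset.** The document gives no entry rate for the joint criterion, no persistence and no incidence, so all three are assumptions here.

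12-month status = entry rate × persistence + (1 − entry rate) × incidence, with incidence of 2% in both groups.

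Example: 0.18 + 0.82 × 0.02 = 0.1964 and 0.08 + 0.92 × 0.02 = 0.0984. The odds ratio is (0.1964/0.8036)/(0.0984/0.9016) = 2.24.

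The last column is the exact rejection probability of the unadjusted continuity-corrected chi-square at 165/385.

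| Entry rate, depressed / not | Persistence | Status at 12 months | OR | Significant |
|---|---|---|---|---|
| 8% / 8% (no imbalance) | 100% | 9.8% / 9.8% | 1.00 | 3% |
| 4.5% / 2% | 60% | 4.6% / 3.2% | 1.48 | 10% |
| 5% / 2.5% | 60% | 4.9% / 3.5% | 1.44 | 9% |
| 4.5% / 2% | 100% | 6.4% / 4.0% | 1.66 | 19% |
| 9% / 4% | 60% | 7.2% / 4.3% | 1.72 | 23% |
| 9% / 4% | 100% | 10.8% / 5.9% | 1.93 | 45% |
| 18% / 8% (ACR alone) | 60% | 12.4% / 6.6% | 2.00 | 54% |
| 18% / 8% (ACR alone) | 100% | 19.6% / 9.8% | 2.24 | 84% |

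The rows with 4.5–9% against 2–4% stand for the joint criterion, which cannot be more frequent than ACR of at least 30 alone.

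**3. Dilution in the other direction.** With equal entry rates of 8%, full persistence and a true doubling of incidence (4% against 2%), status is 0.08 + 0.92 × 0.04 = 0.1168 against 0.0984. The risk ratio is 1.19 instead of 2.

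**4. Power if the endpoint becomes new onset.** Assume 18% and 8% are removed as already positive. This leaves 165 × 0.82 ≈ 135 and 385 × 0.92 ≈ 354 at risk. By the formula in step 1, power is about 50% for incidences of 9% against 4%, 35% for 5% against 2%, 28% for 6% against 3%, 19% for 4% against 2%, and 14% for 3% against 1.5%.

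**The case against.** **Prevalent cases are not explicitly counted.** No sentence says that patients positive at entry count as declined. ACR and eGFR are measured twice, the Discussion speaks of understanding decline from its early phase, and Data analysis names linear regression, which would suit a continuous change. This is a condensed article, and a fuller plan may fix the risk set. It stands that the intention is unknown. But the article does state the definition of the primary endpoint, no change variable is defined anywhere, and the same paragraph reports odds ratios for a binary outcome. This is a definition fixed badly, not a detail left out.

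**The confounder list is open.** This is fair: a reader might infer that baseline renal function will be left out of the model, and the document does not support that. Even age and sex are collected but not named. Adjustment alone, however, would not stop unchanged patients from being labelled as declined.

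**The plan does not assume a baseline imbalance.** A reader might infer one from the 18% and 8%. Sample-size calculations never mentions entry status; it gives these rates as the difference to be detected, drawn from prevalence sources. Treating them as entry rates is an assumption of this check.

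**84% is the top of the range.** It uses ACR alone, full persistence, the largest imbalance and no adjustment. This stands, and it is why a range is given. A claim that the result would mostly reflect baseline disease has no figure behind it for the joint criterion.

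**Conclusion.** The point holds in this limited form: the primary endpoint as written is a 12-month level that does not use baseline, eligibility admits patients who already meet it, and nothing in the document removes them or commits the analysis to baseline ACR or eGFR. It therefore does not answer whether depression predicts decline.

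The direction is clear: any entry difference passes into the result. The size is not known. In the unadjusted comparison with 2% new onset in both groups, the false-positive chance runs from about 3% (no imbalance), through 9–45% (assumed joint-criterion entry rates of 4.5–9% against 2–4%, persistence 60–100%), to 84% as an upper case. Entry rates, persistence and incidence are all assumed.

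**What to change.** Use the baseline values that are already collected.

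1. Define the binary endpoint as new occurrence of the criterion at 12 months among patients who did not meet it at baseline.
2. Alongside it, analyse 12-month log-ACR and eGFR in all patients, with the baseline value as covariate.
3. State that the 18% and 8% derive from prevalences, so the 88% power does not describe a new-onset endpoint, and restate the power on an explicit incidence assumption.

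**Cost.** No new data are needed, but this is more than a change of wording. Patients positive at entry leave the binary analysis, and its power falls clearly (14–50% in the illustrations above), so the sample size has to be reconsidered. The continuous baseline-adjusted analysis keeps all patients. Depression is already present at entry and may have affected renal function before then, so baseline adjustment estimates only the effect after entry; the plan should say that this is the intended question.

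### The stated 88% power is for microalbuminuria alone, but the primary outcome as defined needs raised ACR and reduced eGFR together, which also leaves out the early cases the design is meant to show

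*Protocol article*

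**What the plan says.** Three places in the protocol article bear on this, besides the endpoint section.

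- **Study endpoints:** "The primary outcome is the decline of renal function in four subtypes categorized according to depression and adherence", assessed at 12 months.
- **Renal function:** decline is defined as "ACR ≥ 30 mg/g creatinine and eGFR < 60" (mL/min/1.73 m²). Taken literally, a patient is an event only if both thresholds are crossed.
- **Sample-size calculations:** "550 patients (165 for the depression group and 385 for the non-depression group"), with "a 30 % prevalence of depression", a "10 % difference in microalbuminuria rate (18 % in the depression group and 8 % in the non-depression group"), and "an 88 % chance of detecting a true difference in microalbuminuria at the 5 % level of significance". The test is the continuity-corrected chi-square, and adherence is left out. The planning rates are described as microalbuminuria prevalences. No eGFR rate and no rate for the two conditions together appears.
- **Discussion:** "As an increase of ACR is observed earlier than a decrease of eGFR in CKD", and for that reason the design is said to help in understanding decline from its early phase.

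**The concern.** The defined event and the powered event are not the same. The power calculation uses one marker and the definition uses two. By the Discussion's own account of the order of changes, a patient in the early phase has raised ACR and preserved eGFR. Under the definition as written, that patient has not declined.

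Two things are at stake. First, the study's only power statement does not describe its primary endpoint. The Study endpoints section calls only the secondary analyses underpowered, so a reader will take the primary as covered by the 88%. Second, 'both', 'either' and 'ACR alone' classify different patients as events, so the odds ratios planned in the Data analysis section depend on which is meant.

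**Working it through.** **Inputs from the document (Sample-size calculations).** n₁ = 165 (depression), n₂ = 385 (no depression), p₁ = 0.18, p₂ = 0.08, α = 0.05, chi-square with continuity correction. Sidedness is not stated; two-sided is the reading that reproduces the figure. No dropout allowance is stated and none is applied here.

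**Step 1: reproduce the 88%.**
- Pooled rate: (165 × 0.18 + 385 × 0.08)/550 = (29.7 + 30.8)/550 = 0.11, or about 60 expected events.
- SE under the null: √[0.11 × 0.89 × (1/165 + 1/385)] = 0.02911.
- SE under the alternative: √[0.18 × 0.82/165 + 0.08 × 0.92/385] = 0.03295.
- Continuity correction: ½(1/165 + 1/385) = 0.00433.
- z = (0.10 − 0.00433 − 1.96 × 0.02911)/0.03295 = 1.17, so power = Φ(1.17) = 87.9%.
- Exact enumeration of the corrected test over both binomial distributions gives 88.6%.

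The stated figure is right for microalbuminuria.

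**Step 2: both markers required, illustration only.** Two assumptions are needed that the document does not supply: that microalbuminuria in the sample-size section means ACR ≥ 30 mg/g, and that a common share q of ACR-positive patients in both groups also has eGFR < 60. The rates become 0.18q and 0.08q, and expected events become 60.5q. Exact power of the corrected test at 165/385:

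| q | Depression | No depression | Expected events | Power |
|---|---|---|---|---|
| 1 | 18% | 8% | about 60 | 88.6% |
| 0.7 | 12.6% | 5.6% | about 42 | 73% |
| 0.5 | 9.0% | 4.0% | about 30 | 56% |
| 0.3 | 5.4% | 2.4% | about 18 | 34% |
| 0.2 | 3.6% | 1.6% | about 12 | 23% |

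**Step 3: relax the common q.** Exact power with q in the depression group vs the non-depression group:
- 0.5 vs 0.3 (9.0% vs 2.4%): 86%
- 0.3 vs 0.2 (5.4% vs 1.6%): 58%
- 0.5 vs 0.1 (9.0% vs 0.8%): 99%
- 0.3 vs 0.5 (5.4% vs 4.0%): 8%

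The direction and size of the change in power therefore depend on rates the document does not give.

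**Step 4: either marker suffices ('or').** Let a share g of ACR-negative patients in each group qualify on eGFR alone (assumption). The rates are then 0.18 + 0.82g and 0.08 + 0.92g.
- g = 0.05: 22.1% vs 12.6%, exact power 76%
- g = 0.10: 26.2% vs 17.2%, exact power 64%

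Reading 'and' as 'or' does not restore 88% under these assumptions either.

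**The case against.** The strongest reply is that 'and' is loose wording. The same sentence first uses it to list the two markers assessed, and the second use may simply list one criterion per marker. The early-phase remark in the Discussion fits that reading. This stands as a possibility: the text does not settle what was intended. It does not remove the point, because the primary endpoint would then be misstated and, as Step 4 shows, the 88% would not carry over.

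A reader might also infer that power for the joint endpoint must fall well below 88%. The documents do not support that. They give no joint rate, and the fall shown in Step 2 depends on q being equal in the two groups. Likewise, calling the joint endpoint a subset of the powered one assumes that microalbuminuria means any ACR ≥ 30. The sample-size section gives no ACR range for the term.

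It can further be said that the early phase is not lost to the study: both markers are measured at baseline and at one year (Table 1), clinical variables are secondary outcomes, and the Discussion may refer to measuring ACR rather than to the binary endpoint. That is fair. The loss is confined to the primary classification, where a patient with raised ACR and preserved eGFR is a non-event as the definition is written.

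**Conclusion.** The point holds in this form: the 88% power belongs to microalbuminuria and does not apply to the primary endpoint as defined, and that definition counts as non-events the early cases the Discussion says the design will help to understand. This follows from the text alone. The sample-size arithmetic is correct for the quantity it uses.

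The size of the effect on power is not known. Power of 73% down to 23%, for q from 0.7 to 0.2, is an illustration that rests on a common q and on equating microalbuminuria with ACR ≥ 30. With unequal q, power can stay near 88%, exceed it or fall further. The mismatch concerns the primary endpoint and its only power statement, so it should be resolved before outcomes are analysed.

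**What to change.** Make ACR ≥ 30 mg/g the primary binary criterion, with eGFR < 60 and the combination of the two as secondary. This matches the basis of the sample size and the early-phase rationale. State in the sample-size section that microalbuminuria there means this same ACR criterion.

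If the two-marker definition is kept, say explicitly whether both criteria or either one is required. In each case replace the 88% with power computed from assumed rates for that endpoint in the two groups, with the source of those rates. Under 'or', also report the components separately.

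The cost is a sentence in the Renal function section and, where the endpoint is not ACR alone, a revised power statement. Both markers are already collected at both visits, so no new measurements are needed. The price may be a less favourable stated power.
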